#### User analysis and usability testing analysis

Descriptive statistics will be used to analyse CSUQ an SUS scores according to the formal way of analysis to compare between participant groups (FPs) to take into account gender and age differences [59] in usability. No repeated-measurements neither pre-post test will be analysed.

## Discussion

This pragmatic clinical trial will involve the participation of FPs from over 130 PC health centres in different geographic areas of Spain, thus ensuring a high level of external validity, given that the PC model implemented throughout the country is relatively homogeneous.

Among the possible limitations or biases of our study, we take into consideration that professionals who agree to participate may be more motivated, leading to observer bias (Hawthorne effect). Those professionals more involved in the work will probably make greater use of the DSS than if it were established under normal conditions. If the tool is effective, we might observe an overestimation of the effect that if applied to routine clinical practice would be more limited. This could lead to a greater effectiveness than would be obtained under normal conditions, but it is expected that when randomization is performed after the inclusion of patients in the study, the magnitude of the difference between the two groups will be minimized. Additionally, all physicians will have previously received the training intervention. In this way, it will be ensured that all physicians receive the same training and share the same knowledge of the study, thus reducing performance bias.

The use of a composite endpoint as hospital admission or death is proposed as recommended by some European studies, in order to compare the results with these studies [28, 60, 61].

The intervention cannot be blinded, which could influence the results. However, because the variables can be obtained from records, those who carry out the analysis and their interpretation will not know to which group the patient belongs. In turn, to avoid possible contamination of the professionals in the control group, the intervention group will be advised of their commitment to confidentiality. The control group may use the DSS to review the treatments of the patients included in the study at the end of follow-up for a similar period of time. The expected changes in quality of life are small, but their measurement allows incorporating outcome variables reported by the patient and calculating utilities.

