### Blinding

Due to the type of intervention, neither FPs and their patients nor the MULTIPAP Plus study team was blinded to the treatment allocation.

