### Variables

FPs will provide their data before the start of the study. Patient data will be collected by the recruiting FP, who will also be responsible for patient follow-up. All information will be recorded in a case report form designed for the study. Each FP will access the form from their personal computer through the project website using a personal identification code. Four visits were defined for patient data collection: baseline (T0), 6 months (T1), 12 months (T2), and 18 months (T3) (see Table 1).

**Table 1 Tab1:** Visit plan

	T0 (baseline)		T1 (6 m*)	T2 (12 m*)	T3 (18 m*)	Responsible entity
Confirm inclusion/exclusion criteria	X					FP
Written informed consent	X					FP
Sociodemographic variables	X					FP
Morbidity variables and drug treatment plan	X		X	X	X	FP
Randomization of FP´s		X				RU
FP intervention (intervention group)		X				RT
Patient intervention (intervention group)			X	X	X	FP
Mortality				X	X	RT/FP
Hospitalizations				X	X	RT/FP
Functionality (WHODAS), falls, hip fractures			X	X	X	FP
Use of health services			X	X	X	RT
Quality of life	X			X	X	FP
Usability, adhesion, satisfaction			X		X	TG
Costs					X	RT

*T* time, *FP* family physician, *RU* research unit, *IG* intervention group, *RT* research team, *TG* technical group, *m** months from randomization

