#### Primary outcome variable

The primary outcome is a composite endpoint of hospital admission or death during the observation period measured as a binary outcome. Primary outcome measures are recorded by the FPs when they occur or at follow-up visits.

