##### Trial management committee (TMC)

There will be a principal investigator, a research physician, a statistician, and a administrator at each region. Tasks are as follows: study planning, organization of steering committee meetings, provide annual risk report and ethics committee serious unexpected suspected adverse events, responsible for trial master file, budget administration and contractual issues with individual centres, advice for lead investigators, audit of 6 monthly feedback forms and decide when site visit to occur, assistance with international review and board/independent ethics committee applications, data verification, and randomization (this in Madrid Region).

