#### Composition of the data monitoring committee, its role, and reporting structure

A data monitoring committee (DMC) has been established based on the vital-status outcome measurement chosen and the long trial duration (18 months). The DMC is independent of the study organizers. For the data monitoring committee proposal, we have taken into account the distinguishing characteristics of pragmatic clinical trials [52–54]. This committee includes clinicians, biostatisticians, and ethical experts, and given the patient-centred outcomes focus of our trials [55, 56], a patient representative is incorporated to provide patient’s perspective. This will allow to review relative benefits, burdens, and potential harms of the interventions and will provide insight into the optimal ways for results sharing [57, 58] to participants and relevant patient group.

During the period of recruitment to the study, interim analyses will be supplied, in strict confidence, to the DMC, together with any other analyses that the committee may request. This may include analyses of data from other comparable trials. In the light of these interim analyses, the DMC will advise the TSC. The frequency of interim analyses will depend on the judgement of the Chair of the DMC, in consultation with the TSC. However, we anticipate that there might be one interim analysis at 12 months after randomization and one final analysis at 18 months. The interim analysis will be performed by an independent statistician, blinded for the treatment allocation. The statistician will report to the independent DMC.

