#### Analysis of main effectiveness

The difference in percentages in the composite endpoint of hospital admission or death to 18 months with its corresponding 95% CI. Multilevel analysis will be adjusted considering the combined final variable as the dependent variable; the baseline variables of the patient (first level), the professional (second level), and the intervention group as independent fixed effect variables; and the clustering by physician as a random factor. We will use multiple imputation by chain equations including baseline, 6-month, and 12-month data as available, intervention group, stratification and minimization variables, and other covariates that were informative of missingness. A sensitivity analysis will be conducted to assess whether conclusions may change if assumptions about missing data change.

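### The Discussion claims a masked analysis as mitigation for the open-label design, but the Blinding section excepts no analyst and no masking is stated for the 18-month analysis

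*Protocol article*

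**What the plan says.** The Blinding section of the protocol article reads that "neither FPs and their patients nor the MULTIPAP Plus study team was blinded to the treatment allocation". It excepts no statistician or analyst.

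The Discussion accepts that an unblinded intervention could influence the results. It then offers a mitigation: "those who carry out the analysis and their interpretation will not know to which group the patient belongs". The reason given is "because the variables can be obtained from records".

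On data collection, the Variables section says: "Patient data will be collected by the recruiting FP, who will also be responsible for patient follow-up". The section on the primary outcome says: "Primary outcome measures are recorded by the FPs when they occur or at follow-up visits". Table 1 lists the research team and the family physician (FP) jointly as responsible for mortality and hospitalizations.

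One analyst is described as masked. The section on the data monitoring committee says: "The interim analysis will be performed by an independent statistician, blinded for the treatment allocation". That person reports to the independent committee. The same paragraph anticipates a final analysis at 18 months and says nothing about who performs it or whether they are masked.

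**The concern.** The Discussion presents masked analysis and interpretation as the answer to a known weakness of the design. A reader or a risk-of-bias assessor would credit it as a real safeguard. The section where such a safeguard belongs says that the study team is unblinded and excepts nobody, and the reason given in the Discussion would not produce masking.

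What is at stake is the accuracy of a claimed protection for the primary comparison. If the text stays as it is, the trial report may repeat a safeguard that the plan never set up.

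**Working it through.** No arithmetic applies, and the plan gives no figure on this point to reproduce. The check sets the statements side by side.

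1. **Who is masked.** Blinding section: FPs, patients and the study team are not. Discussion: those who analyse and interpret are. Both can hold only if the analysts are outside the study team, or if they belong to it but receive data with coded arms and have no access to the key. The article states neither for the final analysis.

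2. **Whether the stated reason masks anyone.** An analyst learns the allocation through the group variable, and the primary multilevel model contains that variable as a fixed effect. Masking therefore needs a coded label and a key held elsewhere. Taking outcomes from records does neither. At most it bears on how outcomes are ascertained.

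3. **Whether the reason helps with ascertainment.** The Discussion says only that variables *can* be obtained from records. The Variables and primary outcome sections give the recording to the FP. The Randomization section has each FP told the assigned group before follow-up starts, so the recorder knows the arm. Masking the analyst would not change this.

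4. **How the interim analysis compares.** For the interim analysis the article gives independence, blinding and a reporting line. For the 18-month analysis it gives none of the three. The contrast shows that the arrangement is workable in this trial, and that what is missing is its extension to the final analysis.

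5. **Which analyses the claim could cover.**
   - *Primary analysis: it could.* The listed inputs are the composite outcome, baseline patient variables, FP variables, group and clustering by physician. None exists in one arm only, and a label A/B serves the model as well as the true name.
   - *Cost-utility analysis: it could not.* The rights to use the decision support system (DSS) are charged as a cost of the intervention, so the analyst must know which arm bears them.
   - *DSS usability analysis: it could not.* The data come from FPs who use the tool, and control FPs may use it only after follow-up ends.

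   The Discussion's claim carries no restriction, so it is wider than any masking scheme could deliver.

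**The case against.** The strongest reply is that the article never defines the study team. An analyst outside it, or one given coded arms, would make both statements true. This stands: the two statements can be reconciled, and a reader who infers that one must be false goes further than the text allows. It does not rescue the claim, because the article states no such arrangement for the final analysis and gives a reason that does not supply one.

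A second reply is that a condensed article may leave masking procedures to the full protocol or the analysis plan. This stands for the procedural detail. It does not cover a Blinding section without an exception, or a mistaken reason offered in the article itself.

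Three stronger readings are tempting and are not supported:

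- A reader might infer that the analysts are unblinded because "There will be a principal investigator, a research physician, a statistician, and a administrator at each region" on the trial management committee. The committee's listed tasks do not include outcome analysis, and the article does not equate the committee with the study team.
- A reader might infer that DSS-use data would unmask the primary analysis. Table 1 gives usability to a separate technical group, a separate descriptive analysis is planned for it, and the primary model lists no such field. Such data would reveal the arm only if they were put into the primary dataset.
- A reader might infer from wording such as "other covariates that were informative of missingness" that analysis choices are left open for an unmasked analyst to steer. The analysis plan is not shown and may settle them.

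Finally, hospital admission and death are fairly objective, and no numerical bias has been shown. That stands and limits the weight of the point.

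**Conclusion.** The point holds as a claimed safeguard that the plan does not support. The Blinding section leaves the study team unblinded without exception, the reason given for a masked analysis does not mask anyone, and only the interim statistician is described as blinded. Masking of the 18-month primary analysis is feasible but is not stated.

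The size cannot be put as a number. No estimate, sample size, power or error rate depends on it. The consequence is that the protection credited to the primary comparison may be overstated. Outcome recording by FPs who know their arm would remain even with a fully masked analyst.

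The verdict assumes that the current article text is what readers will rely on, and that no unseen document is needed to make its two statements agree. If the full protocol already names a masked final analyst, the remaining work is to correct the wording and the reason in the article.

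**What to change.** - **Blinding section:** except the analyst of the 18-month primary analysis.
- **Final analysis:** extend the interim arrangement to it. A statistician with no access to allocation works on pseudonymised FP codes and arms labelled A/B. The dataset carries no DSS-only or cost fields. The Research Unit that randomises holds the key until the primary model output is final.
- **Discussion:** limit the masking claim to that analysis, since the cost-utility and DSS usability analyses reveal the arm. Replace the reason based on records with the coding arrangement. State that masking the analyst does not address outcome recording by unblinded FPs.
- **If this is not done:** delete the masking claim from the Discussion.

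The cost is a few sentences, one data-transfer step and a narrower stated safeguard. The article does not show whether any of the regional statisticians is without knowledge of the allocation, so it cannot be assumed that no further person is needed.

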## Trial status

Protocol Version Rev.0 (19.03.2019) + Anexo 2 Rev.0 (05.04.2019). Recruitment started on February 27, 2020. Approximate date for end of recruitment February 28, 2022.

## Abbreviations

FP: Family physician
PC: Primary care
SR: Systematic review
ICT: Information and Communication Technologies
FPs: Family physicians
DSS: Decision support system
eCRF: Electronic case report form
QALY: Quality-adjusted life year
PIP: Potentially inappropriate prescription
